### 2.9. Outcome Measures

#### 2.9.1. Clinical Outcomes

Clinical outcomes (Table 2) to be assessed are:Neurological outcomes, including both sensory function in the mandible and the oral cavity, as well as motor function of cranial nerves that include the facial nerve (VII) marginal branch, hypoglossal nerve (XII), and accessory nerve (XI).Dental status, assessed according to the Eichner classification [21,22].Dental rehabilitation, including use, or potential use, of dental implants or equivalent within the reconstructed mandibular segment (date of placement, number and location of implants, type of healing for dental implants, time to function, dental implant status), as well as dentures (prosthodontic use) if the patient is edentulous or partially edentulous.Survival, including both recurrence-free survival (for OSCC, osteosarcoma, ameloblastoma and oral metastases but not for non-tumour conditions such as bisphosphonate- and/or immunomodulatory drug-induced osteonecrosis) and overall survival (applicable for OSCC, osteosarcoma, ameloblastoma, oral metastases, and non-tumour conditions such as bisphosphonate- and/or immunomodulatory drug-induced osteonecrosis).

#### 2.9.2. Patient-Reported Outcomes

Patient-reported outcomes (Table 2) to be assessed include the Oral Health Impact Profile (OHIP) [23], the EuroQoL five-dimension (EQ-5D-5L) [24] descriptive system, and patient satisfaction.

The OHIP was developed with the aim of providing a comprehensive measure of self-reported dysfunction, discomfort, and disability attributed to oral conditions [23]. The OHIP is concerned with impairment and three functional status dimensions (social, psychological, and physical). Respondents will be asked to indicate on a five-point Likert scale how frequently they experienced each problem within a reference period, for example, 12 months. Response categories for the five-point scale are “very often”, “fairly often”, “occasionally”, “hardly ever”, and “never” [25,26]. The OHIP-14 consists of 14 questions in which higher scores indicate worse outcomes. It has validated translations into several languages; those patients who speak a language for which no validated translation of the OHIP is available will not complete the questionnaire.

The EQ-5D-5L descriptive system comprises five dimensions: mobility, self-care, usual activities, pain/discomfort, and anxiety/depression. Each dimension has five levels: no problems, slight problems, moderate problems, severe problems, and extreme problems. The patient is asked to indicate their health state by ticking the box next to the most appropriate statement in each of the five dimensions. This decision converts into a one-digit number that expresses the level selected for that dimension. The digits for the five dimensions can be combined into a five-digit number that describes the patient’s health state [24].

The patient’s satisfaction with the overall treatment, facial aesthetics, and mouth dryness will be assessed using a five-point Likert scale. Both the EQ-5D-5L [24] and the patient satisfaction questionnaire are available in several languages.

#### 2.9.3. Radiological Outcomes

For the radiological outcomes, available images taken as part of the standard of care will be collected and evaluated centrally by the principal coordinating investigator. The following parameters will be assessed: mandibular dimensions, mandibular continuity, bone quality and quantity in the reconstructed segment, plate geometry/design, and precision of reconstruction. Images collected for this registry could be used for other analyses in the future.

### 2.10. Adverse Events

Because this is an observational registry, only AEs related to the condition and/or the treatments that might have an influence on the outcome will be collected. AE collection will commence as soon as the patient is enrolled. AEs do not need to be immediately reported unless they occur at a higher frequency and/or severity than that reported in the literature. The following AEs pertaining to the bone transplant (graft) and dental implants will be recorded: non-union or pseudarthrosis, malunion, bone sequestration, deep bone infection, osteo(radio)necrosis, total graft/transplant loss, insufficient anastomosis, and loss of dental implants within the reconstructed mandibular segment. The following AEs pertaining to implants and hardware will be recorded: hardware exposure, loosening and breakage, and screw loosening. For soft tissues, the following AEs will be recorded: wound dehiscence, superficial infection, loss of tissue flap or skin paddle, and neurosensory disturbances. General AEs to be collected include AEs related to adjuvant therapy; revision surgery for any other cause; any other AE related to the treatment of OSCC, osteosarcoma, ameloblastoma, osteonecrosis, and other oral metastases or mandibular reconstruction; and donor site morbidity for osseous flaps.

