### 2.4. Recruitment

A recruitment period of 3 years (36 months) is planned to enrol 300 eligible patients. Patient enrolment will be consecutive and competitive (i.e., with no limit in the number of patients enrolled at each site). Potentially eligible patients will be identified by an investigator and/or adequately trained member of the research team at the sites based on the patients meeting all the inclusion and none of the exclusion criteria, ideally after initial pathological/histologic diagnosis of mandibular involvement by oral tumours (such as OSCC, osteosarcoma, and ameloblastoma), bisphosphonate- or immunomodulatory drug-induced osteonecrosis, and mandibular lesions from metastatic diseases have been confirmed and the patients have been scheduled for surgery.

If a patient wishes to participate, a designated member of the research team will explain the informed consent process, including the purpose of the registry, the procedures, the potential risks and benefits, alternatives to participation, and data protection. Patients will also be informed about the possible future use of their de-identified data collected from the current registry for future research projects. Each patient choosing to participate will then sign and date an informed consent form. Consent will be obtained, where possible, before mandibular resection; if it is not possible (from the patient or the surrogate), the patient may provide consent after treatment up until the first standard-of-care follow-up visit, given the purely observational nature of the registry.

All patients who provided consent will be allocated a unique patient number. Each site will keep an Identification List linking patient numbers with their personal information. This Identification List will always be kept safe and in a locked place. Sites will not be allowed to share the Identification List with any third party except for the sponsor representative, legal authorities, and EC/IRB, who may have access to the Identification List during monitoring or auditing activities performed on-site. Figure 1 shows the planned patient flow.

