### 2.11. Statistical Considerations

The registry is exploratory in nature and thus not a hypothesis-driven clinical study. Therefore, no primary or secondary outcomes have been defined. Consequently, and in line with the exploratory nature of registries, no formal sample size or power calculation was performed. The proposed number of patients to be included in the registry (300) was estimated based on the number of patients who could feasibly be enrolled during the planned 3-year enrolment phase and was not based on a statistical hypothesis.

A detailed statistical analysis plan (SAP) will be prepared before the final analysis (i.e., the analysis from which the results will be summarised in the final registry report). The first final analysis will be done when 300 eligible patients have been enrolled and all follow-up visits have been completed. Generally, descriptive statistics will be generated for patient characteristics, clinical data, and outcomes recorded at standard of care scheduled follow-up assessments. Categorical outcomes will be summarised using frequency and percentage for each category. Continuous outcomes will be summarised using mean, standard deviation, median, interquartile range, and minimum and maximum. These summary statistics will also be presented according to clinically relevant categories, e.g., according to treatment pattern.

AEs will be summarised at both the patient level and the AE level. For the analysis on the patient level, multiple events of the same type will be combined for each patient, thus counting each patient with at least one AE only once. AE rates with 95% confidence intervals will be calculated. When calculating event rates, the denominator will be the total population size, irrespective of dropouts during follow-up.

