Generally, all eligible patients who commenced treatment within the registry (i.e., having mandibular resection ≥2 cm and receiving reconstruction within 18 months after mandibular resection) will be included in the analysis. If a patient drops out, data collected up until that point will be included in the analysis. For specific research questions, only certain subgroups of patients may be relevant, and this will be predefined before the analysis. Depending on the amount and quality of the collected data, further appropriate statistics will be applied. Information on the analysis populations, the criteria for inclusion, the handling of missing data, and protocol violations will be defined and specified in the SAP.

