	Visit 1	Visit 2	Visit 3	Visit 4 *	Visit 5 *	Visit 6 *	Visit 7 *	Visit 8 *	2nd Stage Recon	Post 2nd Stage Reconstruction Visits ^1^
	Screening/Preoperative	Intraoperative (Day 0)	Discharge	3 Months (±2 Weeks)	6 Months (±1) Month	12 Months (±2) Months	18 Months (±2) Months	2 Years (±3) Months	Intraoperative (Day 0′)	3 Months (±2 Weeks) 6 Months (±1) Month 12 Months (±2) Months 18 Months (±2) Months 2 Years (±3) Months
**Patient information/consent**	X									
**Eligibility**	X									
**Baseline characteristics**	X									
**Tumour/osteonecrosis of mandible characteristics**	X									
**Adjuvant treatment for the malignant conditions (OSCC, Osteosarcoma of mandible, Malignant ameloblastoma, Oral metastases) ^2^**			X							

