**Patient-reported outcomes**										
**OHIP**	X		X	X	X	X	X	X		X
**EQ-5D-5L**	X		X	X	X	X	X	X		X
**Patient satisfaction**					X	X	X	X		X
**Adverse events**		X	X	X	X	X	X	X	X	X
**Radiological assessment ^5^**	X	X	X	X	X	X	X	X	X	X

* Postoperative FU visits with the defined time windows are calculated from the day of mandibular resection (i.e., day 0) and reconstruction (if the patient undergoes primary reconstruction).^1^ Post-second-stage reconstruction visits will be calculated from the day of secondary reconstruction (day 0). Patients will be followed up for a maximum of 2 years from the time of mandibular resection. ^2^ Information on adjuvant treatment for the malignant conditions may be available at a different timepoint and will be documented whenever it becomes available. ^3^ Osseous reconstruction can occur on the day of resection (one-stage reconstruction) or on a different day (two-stage reconstruction). ^4^ Additional surgeries may occur at any time after mandibular resection. ^5^ All images will be taken according to the local standard of care and will be collected. Assessments will be performed on available images.

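### The start of AE collection (enrolment, in 2.10) conflicts with Table 3 (day 0) for patients who consent after surgery, so early AE rates could be too low

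*Protocol article*

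**What the plan says.** Four parts of the protocol article bear on the point.

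- **Consent (2.4).** The rule is "Consent will be obtained, where possible, before mandibular resection". If that cannot be done, "the patient may provide consent after treatment up until the first standard-of-care follow-up visit". The patient number is allocated only to those who have consented, so enrolment is reasonably read as following consent, although the article does not define the word.
- **AE start (2.10).** "AE collection will commence as soon as the patient is enrolled". Nothing is said about events that happened before that moment.
- **Schedule (Table 3).** The row "Adverse events" is marked in every column except Visit 1. It therefore includes Visit 2, whose label begins "Intraoperative (Day 0", and Visit 3 (discharge). Consent is marked only at Visit 1, so the table describes the usual route and does not mention late consent.
- **Analysis (2.11).** "AE rates with 95% confidence intervals will be calculated", and for these "the denominator will be the total population size, irrespective of dropouts during follow-up". The analysis population is eligible patients "having mandibular resection ≥2 cm and receiving reconstruction within 18 months after mandibular resection". The timing of consent is not a criterion, so late consenters are counted.

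**The concern.** For a patient who consents after the operation, 2.10 and Table 3 give different starting points for AE collection. One site may follow 2.10 and enter nothing from before consent. Another may follow Table 3 and enter the intraoperative and discharge events from the chart. Both would be complying with the article, and there are 18 sites.

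The events exposed to this are on the registry's own list in 2.10: insufficient anastomosis, loss of a tissue flap or skin paddle, wound dehiscence and superficial infection can all occur early. If they are omitted for some patients who remain in the denominator, the rate is biased downward, and the planned 95% confidence interval does not reflect that bias.

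The loss would also be uneven. In a one-stage case the bone graft is placed on day 0, before a late consent. In a two-stage case the osseous reconstruction would usually come after consent, so mainly resection-stage events are exposed. Describing AEs by treatment modality is the second objective in 2.2, and the Introduction and Discussion treat one-stage versus two-stage as an open question. An artefact that favours one-stage surgery would fall on that comparison.

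**Working it through.** The plan has no figure of its own to reproduce. The 300 patients are a feasibility number, no power calculation was done, and no AE rate or late-consent share is given. The arithmetic below only shows how the bias behaves.

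**Inputs**

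- N = 300 (2.4, 2.11).
- p = true share of patients with an AE of a given type. Not given; 20% assumed.
- f = share of patients who consent after surgery. Not given; 5% to 30% assumed. The wording of 2.4 makes late consent the exception, so the lower end is the more natural reading.
- q = among affected late consenters, the share whose only events of that type fall before consent. Not given; 0.5 to 1 assumed.
- AE risk is taken as the same in early and late consenters, and every pre-consent event as unrecorded.

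**Formula**

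Observed rate = p × (1 − f × q). The relative understatement is f × q, whatever p is. It is a ceiling in two respects. Some pre-consent events may still be entered. And 2.11 combines repeated events of one type within a patient, so a patient with a later recorded event of that type is still counted.

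**Results for p = 20%**

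With capture from day 0 for everyone, 60/300 = 20.0% (95% Wilson interval 15.9 to 24.9, half-width about 4.5 points). With pre-consent events omitted:

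| f | q | f × q | Patients missed (60 × f × q) | Observed rate | 95% interval |
|---|---|---|---|---|---|
| 5% | 0.5 | 2.5% | 1.5 | 19.5% | 15.4 to 24.4 |
| 10% | 0.8 | 8% | 4.8 | 18.4% | 14.4 to 23.2 |
| 20% | 0.8 | 16% | 9.6 | 16.8% | 13.0 to 21.4 |
| 30% | 1 | 30% | 18 | 14.0% | 10.5 to 18.4 |

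The absolute loss is 0.5 to 6.0 percentage points. Only in the last row does the interval exclude the true 20%.

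**By treatment pattern**

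Take the same true graft AE risk of 20% in both groups and f = 20%. With q = 0.8 in one-stage cases the observed rate is 0.20 × (1 − 0.16) = 16.8%. With q = 0 in two-stage cases, because the graft follows consent, it stays at 20.0%. The apparent difference of 3.2 points comes from collection alone.

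**The case against.** The strongest reply is that nothing need be lost. Table 3 schedules AE recording at the intraoperative and discharge visits with no exception. The resection and reconstruction data of a late consenter can only be entered from the chart, and AEs could be entered the same way. Section 2.10 can be read as saying when the site's duty begins, not as barring earlier events. The full protocol or the CRF instructions, which the article condenses, may settle this. It follows that a reader who infers from 2.10 that perioperative AEs certainly fall outside collection goes further than the text. What stands is that 2.10 as printed gives a different start from Table 3, and no look-back is stated.

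A second reply is that other items catch some of these events. Additional surgeries are recorded with date and indication (2.5.2), and may occur at any time after resection (Table 3, note 4), so a flap failure that led to reoperation would leave a trace. A dehiscence or infection still present at enrolment would be seen. This narrows the loss, but 2.11 does not say that AE rates draw on those items.

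A third reply is that late consent is a declared exception in an exploratory registry, so f is probably small. That is fair, and it limits the size.

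Two further inferences are tempting and not supported. One is that late consenters' preoperative OHIP and EQ-5D-5L scores would be recalled: the article nowhere provides for recall, and it leaves missing data to the SAP. The other is that survival contains immortal time and needs left truncation: Table 3 counts visit windows from day 0, but no section fixes the time origin for survival, and that choice belongs to the SAP.

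**Conclusion.** The point holds as a conflict between two collection rules, with a possible downward bias in early AE rates. It concerns only patients who consent after surgery, and mainly graft and flap events in one-stage cases. The size cannot be determined from the article. With equal AE risk in early and late consenters, the relative understatement is at most f × q. If late consenters carry a higher risk, the loss could exceed that. Within the assumed ranges, the bias runs from negligible to somewhat more than the sampling error of a rate based on 300 patients.

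It is worth settling in the protocol, because a later SAP can choose analyses but cannot use events that were never collected. With 138 patients enrolled, 118 of them so far eligible (2.13), a look-back is still feasible.

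**What to change.** Align 2.10 with Table 3. Suggested wording: AEs are recorded from day 0 (resection) for every patient; for patients who consent after surgery, AEs before consent are taken from the medical record.

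In addition:

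- Record the consent date and flag patients who consented after surgery.
- Apply the rule to late consenters already enrolled, where the consent given and the local ethics approval allow it.
- Report early AE rates with and without late consenters, overall and by one-stage or two-stage reconstruction.

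The cost is one changed sentence, one date field with a flag, and a short chart abstraction for late consenters. Events taken from charts may be less complete than those recorded prospectively, which is why the rates should be shown both ways.

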### 2.11. Statistical Considerations

The registry is exploratory in nature and thus not a hypothesis-driven clinical study. Therefore, no primary or secondary outcomes have been defined. Consequently, and in line with the exploratory nature of registries, no formal sample size or power calculation was performed. The proposed number of patients to be included in the registry (300) was estimated based on the number of patients who could feasibly be enrolled during the planned 3-year enrolment phase and was not based on a statistical hypothesis.

A detailed statistical analysis plan (SAP) will be prepared before the final analysis (i.e., the analysis from which the results will be summarised in the final registry report). The first final analysis will be done when 300 eligible patients have been enrolled and all follow-up visits have been completed. Generally, descriptive statistics will be generated for patient characteristics, clinical data, and outcomes recorded at standard of care scheduled follow-up assessments. Categorical outcomes will be summarised using frequency and percentage for each category. Continuous outcomes will be summarised using mean, standard deviation, median, interquartile range, and minimum and maximum. These summary statistics will also be presented according to clinically relevant categories, e.g., according to treatment pattern.

AEs will be summarised at both the patient level and the AE level. For the analysis on the patient level, multiple events of the same type will be combined for each patient, thus counting each patient with at least one AE only once. AE rates with 95% confidence intervals will be calculated. When calculating event rates, the denominator will be the total population size, irrespective of dropouts during follow-up.

Generally, all eligible patients who commenced treatment within the registry (i.e., having mandibular resection ≥2 cm and receiving reconstruction within 18 months after mandibular resection) will be included in the analysis. If a patient drops out, data collected up until that point will be included in the analysis. For specific research questions, only certain subgroups of patients may be relevant, and this will be predefined before the analysis. Depending on the amount and quality of the collected data, further appropriate statistics will be applied. Information on the analysis populations, the criteria for inclusion, the handling of missing data, and protocol violations will be defined and specified in the SAP.

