## 1. Introduction

Mandibular defects requiring reconstruction are common and occur after treatment of primary diseases, such as resection of benign or malignant lesions, inflammation, osteo(radio)necrosis, or as a result of trauma [1,2,3]. Management and reconstruction of segmental mandibular defects is challenging, as these defects can lead to severe dysfunction, facial disfigurement, and reduced quality of life, among others [4]. Segmental mandibular defect reconstruction (SMDR) is required to reconstruct the defect with the aim to restore function and aesthetics [5,6]. Manifold options exist for SMDR, including different graft types, donor sites, types of plates, and materials [7]. For transplanted bone grafts, the position, quality and quantity of transplanted bone into the mandible are crucial for later dental rehabilitation, which is one of the priorities in the restoration of functionality. After SMDR, it is known that the number of dentally rehabilitated patients is quite low (15–20%) [8,9,10,11], which is also reflected in our clinical experience, yet few studies describe the rates of and barriers to implant completion after resection. Pogrel et al. reported that 20% to 24% of patients who had osseous reconstruction of mandibular defects went on to have implants, but the reasons why patients did not have implants were not explored [12].

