### 2.8. Termination of Participation

Participation in this registry may terminate early for reasons such as withdrawal of informed consent, the patient being found to be ineligible, investigator’s discretion (e.g., patient noncompliance), no osseous reconstruction with autologous bone performed within 18 months from resection, loss to follow-up, death, sponsor’s decision, or other reasons. Early terminations will be recorded in a dropout form, including the circumstances leading to the termination. All patient data collected before termination will be censored as of the day of the official withdrawal. Censored data will be included in the analysis, unless a patient explicitly requested removal of their data.

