Many clinical questions remain in the present clinical landscape. These include the known limitations of donor sites; specifically, it is unclear how donor site morbidity influences the prolonged rehabilitation of patients undergoing reconstruction following segmental mandibular resection. Further, it is unclear whether the QoL of patients undergoing two-stage reconstruction is improved if a longer rehabilitation process is avoided. The primary endpoint of a reconstruction should be the ability to offer all patients a dental rehabilitation protocol, yet in the present treatment environment, only 15–20% of SMDR patients receive dental implants [8,9,10,11,12]. Moreover, mandibular reconstruction following tumour/mandibular resection poses notable challenges for treatment outcomes, particularly due to limitations inherent in both one-stage and two-stage osseous reconstruction techniques. One-stage reconstruction enables faster restoration but may result in suboptimal outcomes due to intraoperative difficulties in accurately contouring the graft, especially in complex defects, leading to impaired dental rehabilitation, aesthetic compromise, and increased flap failure risk. Two-stage reconstruction facilitates more effective treatment planning for complex defects and allows a period of bone adaptation before the final reconstruction but delays rehabilitation, increases infection and scarring risks, and often requires multiple interventions, adversely affecting recovery and overall clinical outcomes. Another aspect of this study will be to investigate the extent to which the principal goal of mandibular bone reconstruction can be realised and the cumulative surgical, prosthodontic, and logistical demands involved before achieving functional or even theoretically viable dental rehabilitation. This study has a two-year follow-up period; although it may not be sufficient to evaluate long-term outcomes, it will allow assessment of whether the reconstruction can be used for a dental implant and dental rehabilitation protocol. Any such dental rehabilitation should ideally take place within a time period of up to two years after the segmental defect reconstruction.

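### Dividing every adverse event count by the total population turns implant loss into a burden per registry patient, not a risk, and modestly understates late events when patients are lost

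*Protocol article*

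**What the plan says.** Section 2.11 of the protocol article plans patient-level AE summaries in which "multiple events of the same type will be combined for each patient, thus counting each patient with at least one AE only once". It adds that "AE rates with 95% confidence intervals will be calculated" and then fixes the denominator: "When calculating event rates, the denominator will be the total population size, irrespective of dropouts during follow-up". That sentence covers all AE types.

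Section 2.10 lists "loss of dental implants within the reconstructed mandibular segment" among the events to be recorded. On how many patients can have that event, the article gives two figures. The Discussion says that "only 15–20% of SMDR patients receive dental implants", and the Introduction cites a report that "20% to 24% of patients who had osseous reconstruction of mandibular defects went on to have implants".

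Section 2.8 expects early termination for reasons that include "no osseous reconstruction with autologous bone performed within 18 months from resection, loss to follow-up, death, sponsor’s decision, or other reasons". It censors such patients at withdrawal but keeps their data in the analysis.

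Section 2.11 also limits the analysis, in general, to patients with a resection of at least 2 cm who were reconstructed within 18 months. It allows predefined subgroups for specific research questions and leaves analysis populations and missing data to the SAP.

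**The concern.** A proportion estimates a risk only if everyone in the denominator could have had the event and was watched long enough for it to be seen. The rule in section 2.11 breaks both conditions.

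- **Exposure.** A patient without a dental implant cannot lose one. Such patients add to the denominator and never to the numerator, so the reported figure is the implantation rate multiplied by the loss risk among recipients.
- **Observation.** A patient who withdraws or is lost at month 3 is treated as if known to be event-free to month 24.

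The second objective (section 2.2) is to describe outcomes and AEs by treatment modality, and section 2.11 presents summaries by treatment pattern. If modalities differ in how often implants are placed, or in how many patients are lost, the reported AE rates will differ even where the underlying risks are equal. The Discussion treats dental rehabilitation as the main goal of reconstruction, so implant loss is not a minor line in the table.

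**Working it through.** The article states no AE rate, so there is no figure to reproduce. The checks below take the rule as written.

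**1. Implant loss**

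Inputs: planned N = 300 (section 2.4); share with implants s = 15–20% (Discussion) or 20–24% (Introduction). The loss risk r among recipients is not given and is assumed.

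Reported proportion = s × r, so the understatement factor is 1/s, whatever N and r are:

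- s = 0.15: 1/0.15 = 6.7
- s = 0.20: 1/0.20 = 5.0
- s = 0.24: 1/0.24 = 4.2

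Of 300 patients, 45, 60 or 72 would be recipients. An assumed r of 10% would be reported as 1.5%, 2.0% or 2.4%. Even if every recipient lost an implant, the reported rate could not exceed s.

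Illustration with exact (Clopper–Pearson) 95% intervals, 52 recipients (52/300 = 17.3%) and 5 patients with a loss:

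| Denominator | Estimate | 95% CI |
|---|---|---|
| Recipients, 5/52 | 9.6% | 3.2–21.0% |
| All patients, 5/300 | 1.7% | 0.5–3.8% |

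The second interval is narrow because it describes a different quantity. It does not contain the estimate among recipients.

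Between groups: if two modalities share r = 10% but place implants in 15% and 24% of patients, the reported rates are 0.15 × 10% = 1.5% and 0.24 × 10% = 2.4%. The whole difference comes from how many implants were placed.

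**2. Withdrawal and loss to follow-up**

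Assumptions, none of them in the article: a true 24-month risk R = 20%; a constant hazard h = −ln(1 − R)/24 = 0.0093 per month; a fraction d lost independently of the event, at times uniform over 0–24 months.

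Reported proportion = (1 − d)R + d × m, where m is the mean of 1 − exp(−hu) for u uniform on 0–24. Then m = 1 − R/(24h) = 1 − 0.20/0.2231 = 0.104.

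- d = 0.20: 0.80 × 0.20 + 0.20 × 0.104 = 18.1%
- d = 0.30: 0.70 × 0.20 + 0.30 × 0.104 = 17.1%
- d = 0.40: 0.60 × 0.20 + 0.40 × 0.104 = 16.1%

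With a constant loss hazard instead of uniform loss, the figures are 18.0%, 16.9% and 15.8%. The relative understatement is roughly 10–21%. It would be smaller for events that cluster soon after surgery, such as wound dehiscence or failure of the anastomosis.

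**The case against.** **The SAP could put this right.** The sentence names only dropouts, the SAP is still to come, and section 2.11 allows predefined subgroups. It is true that the exposure point follows from the words on total population and is not spelled out, and event-specific populations are not forbidden. But the subgroup and SAP clauses are general, and neither is tied to AE rates. The denominator sentence is specific, and an SAP that follows it inherits the problem.

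**Total N is a legitimate quantity, and no data are lost.** Both points stand. Loss per registry patient is a valid burden measure. Section 2.9.1 also collects implant placement dates, numbers and status, so loss among recipients can be computed. The problem is a single figure presented as the event rate.

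**The dropout effect is small.** At 20% loss, 18.1% lies well inside the exact interval for 60/300 (15.6–25.0%). That also stands. It is a secondary reason for change, and it rests on assumed dropout.

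**Stronger readings that the article does not support:**

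- *Deaths counted as event-free bias the rates.* Under cumulative incidence with death as a competing event, a patient who dies first has no later event, and keeping that patient in the denominator is correct. Only withdrawal and loss to follow-up matter here.
- *Graft events are diluted in the same way as implant loss.* The analysis set is already limited to reconstructed patients, so dilution by unexposed patients is minimal. Section 2.10 lists no event specific to a second stage.
- *The denominator makes two-stage reconstruction look safer.* With the second stage at month 12 and the hazard used above, two-stage patients would show 10.6% against 20%. But that gap comes from shorter observation after reconstruction, under an assumed interval and a constant hazard. At a 3-month interval it would be 17.7%. Unequal observation needs handling, but it is a separate matter from the denominator.

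**Conclusion.** The point holds for AEs that need a prior exposure and, to a lesser degree, for late AEs.

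For implant loss, the rule as written understates the risk among recipients about 4.2- to 6.7-fold. This rests only on the article's 15–24% range for implant receipt and needs no dropout assumption. Other conditional events, such as those of adjuvant therapy or soft tissue flaps, are affected in the same direction, but the article gives no shares from which to size the effect.

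For late events, the added understatement is modest: a true 20% reported as about 18–16% at assumed losses of 20–40%.

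The registry is descriptive, has no primary outcome and collects the dates needed, so this is a should-fix matter. It does not threaten the study.

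**What to change.** Replace the denominator sentence in section 2.11, and carry the replacement into the SAP, so that:

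1. Each AE is analysed in the patients at risk for it. Implant loss is analysed among patients with an implant in the reconstructed segment, timed from placement; other conditional events are handled likewise.
2. Late AEs are reported as cumulative incidence (Aalen–Johansen) with death as a competing event, censoring at last contact, and 95% confidence intervals.
3. Graft AEs are timed from osseous reconstruction, and one- and two-stage groups are compared only at a horizon that both reach. The Table 3 footnote caps follow-up at 2 years from resection, while the same table lists visits to 2 years after the second stage. These must be reconciled first. Under the cap, a 24-month incidence from reconstruction cannot be estimated for two-stage patients, who have only 24 months minus the interval between operations.
4. The proportion over all patients is kept as a supplementary column, labelled as burden per registry patient.

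The cost is a paragraph of wording and a little more analysis. Procedure dates, implant placement dates and dropout records are already collected. Intervals for conditional events will be wider and the rates less favourable. The change should be settled before the analysis planned for May–September 2026.
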